**Equity**

Substantial population-level sexual health impacts, for example on teenage pregnancy and DRV, cannot be achieved via targeted interventions;(19, 49) therefore Positive Choices is a universal intervention. Nonetheless, the intervention aims to maximally benefit disadvantaged and minority students by addressing the more upstream determinants of sexual health, such as engagement with school and gender and other social norms, and by ensuring that disadvantaged and minority students are involved in and reached by intervention activities such as school health promotion councils and social-marketing campaigns. Research methods will also be inclusive for disadvantaged and minority students, for example using fieldworkers from diverse backgrounds, using plain written English materials and supporting all students who need help in surveys and other data collection. Our primary outcome and most of our secondary outcomes are inclusive with regard to gender and sexual orientation. We will assess how intervention reach, acceptability and effects vary by student gender, sexual orientation, ethnicity and SES, and by school-level measures of GCSE attainment and local deprivation. Student recruitment to qualitative research will be purposive by gender and ethnicity. It will not be feasible in schools to purposively sample students by sexual orientation or socio-economic status but we will strive to be inclusive of a diversity of students.

**Knowledge exchange and dissemination**

Our knowledge exchange will be informed by consultation at the end of the study with the ALPHA young researchers’ group as well as with our group of policy/practitioner stakeholders. As well as reporting in the NIHR Public Health Research journal, we will submit two open-access papers to top journals. Authorship will follow International Committee of Medical Journal Editors guidance. We will present our findings at two international conferences (Society of Prevention Research; International Association for Adolescent Health), plus national academic and policy conferences. We will disseminate the results to participating schools, the ALPHA group and the policy/practice stakeholder group. We will draft an article for the Times Education Supplement about the research. The research team will also use blog-posts and Twitter to increase public awareness of the study. A policy and practice dissemination event will be held at SEF targeting the central and local government, education, public health and voluntary sectors. The most important scientific outputs generated by this project will be evidence about the effectiveness, costs and potential scalability and transferability of a whole-school social-marketing intervention to promote sexual health. If this trial finds that Positive Choices is effective in reducing non-competent first sex, this would be scaled up by SEF working collaboratively with the investigators, marketing the intervention to secondary schools, local authorities, school networks and academy chains who would be charged by SEF to be trained to deliver the intervention. Background intellectual property for the intervention lies with LSHTM. Foreground intellectual property for additional intervention materials and the outputs of the research will lie with LSHTM, which will grant the collaborating institutions licence to use these materials in teaching and training activities. Licence to use the intervention materials in scaled up delivery will be contingent on the evaluated effectiveness of the intervention.

**Availability of data and materials**

Data will be made available after the main trial analyses have been completed on reasonable request from researchers with ethics approval and a clear protocol.

**SUPPLEMENTARY MATERIALS 2: AREAS OF SCHOOL RECRUITMENT**

Bath and North Somerset

Berkshire

Buckinghamshire

Cambridgeshire

Cheshire

Bedfordshire

Bristol

Derbyshire

Dorset

East Sussex

Essex

Gloucestershire

Hampshire

Herefordshire

Hertfordshire

Kent

Leicestershire

Lincolnshire

Liverpool

London

Manchester

Norfolk

Northamptonshire

Nottinghamshire

Oxfordshire

Rutland

Shropshire

Somerset

Staffordshire

Suffolk

Surrey

Warwickshire

West Midlands

West Sussex

Wiltshire

Worcestershire

**SUPPLEMENTARY MATERIALS 3: MEASURES**

| **Measure** | **Variable type: binary, continuous or categorical** | **Items** | | | | **Additional coding for multi-item measure** | **Original source** |
| --- | --- | --- | --- | --- | --- | --- | --- |
|  |  | **Sample for question** | **Question wording** | **Response options** | **Question coding** |  |  |
| Family affluence | Continuous | All | Do any of the adults you live with own a car, van or truck? | 1 - No  2 - Yes, one car or van  3 - Yes, two or more cars or vans | Numerical scores 0-n  per item for response options 1-n with higher scores  indicating more affluence | Scores then summed | Family affluence scale^1^ |
|  |  |  | Do you have your own bedroom to yourself at home? | 1 – No  2 - Yes |  |  |  |
|  |  |  | How many computers do the family members you live with own (including laptops and tablets but not including game consoles or smartphones)? | 1 - None  2 - One  3 - Two  4 - More than two |  |  |  |
|  |  |  | How many bathrooms (rooms with a bath or shower) are in your home? | 1 - None  2 - One  3 - Two  4 - More than two |  |  |  |
|  |  |  | Do you have a dishwasher at home? | 1 – No  2 - Yes |  |  |  |
|  |  |  | During the past 12 months, how many times did you and your family travel out of the United Kingdom (UK) for a holiday/vacation? | 1 - None  2 - One  3 - Two  4 - More than two |  |  |  |
| University expectations | Binary | All | By the time you are 20 years old, do you think you will:  1. Be in a steady job?  2. Be in a job training scheme or apprenticeship?  3. Be at university?  4. Be at college studying for a trade or job? | 1-Definitely will  2-Probably will  3-Probably will not  4- Definitely will not | Scored 1 if item 3 ticked and 0 if not | NA | RIPPLE^2^ |
| School belonging | Continuous | All | How much do you agree with the following statements?  1. I feel very different from most other students here  2. I can really be myself at this school  3. Other students in this school take my opinions seriously  4. I am encouraged to express my own views in my classes  5. Most of the students in my classes enjoy being together  6. Most of the students in my classes are kind and helpful  7. Most other students accept me as I am  8. I feel I belong at this school | 1- No, totally disagree  2- No, I don’t really agree  3 - Yes, I agree a bit  4- Yes, totally agree | Each item scored 1 for option 1 to 4 for option 4 with higher scores indicating more engagement in school. | Scores across items summed . Counted as missing if >2 items missing. If 2 or fewer items missing then mean calculated for completed items. | Beyond Blue School Climate Questionnaire^3^ |
| Educational commitment | Continuous | All | How much do you agree with the following statements?  1. I try hard in school  2. Doing well in school is important to me  3. Continuing or completing my education is important to me  4. I feel like I am successful in this school | 1- No, totally disagree  2- No, I don’t really agree  3 - Yes, I agree a bit  4- Yes, totally agree | Each item scored 1 for option 1 to 4 for option 4 with higher scores indicating more engagement in school. | Scores across items summed . Counted as missing if >2 items missing. If 2 or fewer items missing then mean calculated for completed items. | Beyond Blue School Climate Questionnaire^3^ |
| School participation | Continuous | All | How much do you agree with the following statements?  1. There are lots of chances for students at this school to get involved in sports, clubs and other activities outside class  2. Teachers at this school notice when students are doing a good job and let them know about it  3. At this school, students have a lot of chances to help decide and plan school activities, events and policies  4. Student activities at this school offer something for everyone  5. Students have a say in decisions affecting them at this school  6. Students at this school are encouraged to take part in activities, programmes and special events | 1- No, totally disagree  2- No, I don’t really agree  3 - Yes, I agree a bit  4- Yes, totally agree | Each item scored 1 for option 1 to 4 for option 4 with higher scores indicating more engagement in school. | Scores across items summed . Counted as missing if >2 items missing. If 2 or fewer items missing then mean calculated for completed items. | Beyond Blue School Climate Questionnaire^3^ |
| Teacher relationships | Continuous | All | How much do you agree with the following statements?  1. The teachers at this school are fair in dealing with students  2. There’s at least one teacher or other adult in this school I can talk to if I have a problem  3. I feel I can go to my teachers with the things that are on  my mind  4. In this school, teachers believe all students can learn  5. In this school, students’ ideas are listened to and valued  6. In this school, teachers and students really trust one another  7. In this school, teachers treat students with respect  8. This school really cares about students as individuals  9. Most of my teachers really listen to what I have to say  10. I really like most of my teachers at this school | 1- No, totally disagree  2- No, I don’t really agree  3 - Yes, I agree a bit  4- Yes, totally agree | Each item scored 1 for option 1 to 4 for option 4 with higher scores indicating more engagement in school. | Scores across items summed . Counted as missing if >2 items missing. If 2 or fewer items missing then mean calculated for completed items. | Beyond Blue School Climate Questionnaire^3^ |
| Depressive symptoms (PHQ-8) | Continuous | All | How often have you been bothered by each of the following symptoms during the past two week?  1. Feeling down, depressed, irritable, or hopeless?  2. Little interest or pleasure in doing things?  3. Trouble falling asleep, staying asleep, or sleeping too much?  4. Poor appetite, weight loss, or overeating?  5. Feeling tired, or having little energy?  6. Feeling bad about yourself – or feeling that you are a failure, or that you have let yourself or your family down?  7. Trouble concentrating on things like school work, reading, or watching TV?  8. Moving or speaking so slowly that other people could have noticed? Or the opposite – being so fidgety or restless that you were moving around a lot more than usual? | 1. Not at all  2. Several days  3. More than half the days  4. Nearly every day | Each item scored 0 for option 1 to 3 for option 4 with higher scores indicating more depressive symptoms. | Scores across items summed . + | Patient Health Questionnaire (PHQ-8)^4^ |

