
Secondary outcomes will examine other important potential benefits:

- age at sexual debut, using an adapted version of the RIPPLE measure;(72)
- non-use of contraception at first and last sex among those reporting heterosexual intercourse, using an adapted version of the RIPPLE measure;(72)
- number of sexual partners, using an adapted RIPPLE measure;(72)
- dating and relationship violence (DRV) victimisation (including non-volitional sex) measured using an adapted version of the short Conflicts in Adolescent Dating Relationships Inventory (sCADRI) scale which is widely used and was piloted for reliability in our recent Project Respect study (ordinal alpha=0.89);(42, 73, 74)
- sexually transmitted infections (STIs), focused on self-reported diagnosis with common infections, using an adapted version of the RIPPLE measure;(72)
- pregnancy and unintended pregnancy for girls and initiation of pregnancy for boys using adapted versions of the RIPPLE measures.(72)

*Intermediate outcome measures:* We will not undertake mediation analysis because this requires two waves of follow-up, which is not planned in the interests of minimising costs and maximising school retention. It is our experience across studies that multiple follow-ups reduce rather than maintain school engagement and hence response rates.(52) However, informed by our theory of change,(64, 65) we will undertake exploratory analyses of intervention effects on the following ‘intermediate’ outcomes(75) using existing measures(36, 39, 51, 76) tested for reliability in our pilot (ordinal alphas indicated below for multi-item scales): school-level social norms supportive of healthy relationships and sexual health (alpha=0.77); individual-level attitudes towards DRV (alpha=0.65) and gender roles (alpha=0.68); individual-level school engagement (alpha=0.74); career/educational aspirations; sexual health knowledge (alpha=0.78); sexual health and contraceptive skills (alpha=0.92); sexual communication self-efficacy (alpha=0.93); and communication with parents; sexual and reproductive health services access (alpha=0.83) DRV perpetration (including non-volitional sex) measured using sCADRI (ordinal alpha=0.88); and sexual harassment.(77)

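### Three scoring rules in Supplementary materials 3 give wrong or contradictory scores if applied as written

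*Combined protocol and SAP*

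**What the plan says.** The measures table in Supplementary materials 3 gives the same scoring to School belonging (8 items), Educational commitment (4), School participation (6) and Teacher relationships (10). The item rule is "Each item scored 1 for option 1 to 4 for option 4 with higher scores indicating more engagement in school". The scale rule is "Scores across items summed . Counted as missing if >2 items missing", followed by "If 2 or fewer items missing then mean calculated for completed items". No step multiplies that mean back up or uses it to fill the blank items.

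Item 1 of School belonging reads "I feel very different from most other students here" and item 8 reads "I feel I belong at this school". Both fall under the one item rule, and no reversal is stated.

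University expectations is a binary variable built from item 3 of a four-item question. Each item has four response levels, the last being "4- Definitely will not". The coding is "Scored 1 if item 3 ticked and 0 if not".

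**The concern.** Each rule, followed literally, produces a score that does not mean what the table says it means.

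- **Sum and mean.** Students with one or two blank items are placed on a 1 to 4 scale beside classmates on a scale that runs up to 16, 24, 32 or 40. They would look extremely disengaged because they skipped an item.
- **Unreversed item.** One of the eight School belonging items works against the other seven.
- **University expectations.** The variable would separate students who answered the item from those who left it blank, whatever their answer.

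All five variables are exposures in the models of Supplementary materials 6. A reader who wants to interpret or reproduce those coefficients needs to know the scale behind them.

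**Working it through.** The documents report no figure that depends on these rules and could be reproduced first, so the check applies the rules as written.

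**1. Sum against mean.** With k items scored 1 to 4, the sum runs from k to 4k, and a mean of completed items runs from 1 to 4. Take a student who answers 3 to every item.

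| Scale | k | Range of sum | Complete data | One item blank, as written | Mean × k |
| --- | --- | --- | --- | --- | --- |
| School belonging | 8 | 8–32 | 24 | 3 | 24 |
| Educational commitment | 4 | 4–16 | 12 | 3 | 12 |
| School participation | 6 | 6–24 | 18 | 3 | 18 |
| Teacher relationships | 10 | 10–40 | 30 | 3 | 30 |

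On every scale the 3 lies below the lowest score possible with complete data. Zero missing items also satisfies the condition of two or fewer, so a complete responder is told to take both a sum and a mean.

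The scale matters for reading the results. The unimputed student-level coefficient for School belonging in Supplementary materials 6 is -0.29. Across the full range this is 24 × 0.29 = 7.0 outcome units if the score is a sum, and 3 × 0.29 = 0.9 if it is a mean.

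*Illustration with assumed inputs.* Suppose School belonging has mean 24 and SD 4, and a fraction f of students miss one or two items and receive one eighth of their full score.

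- Variance = (1-f)·4² + f·(4/8)² + f(1-f)·(24-3)².
- At f = 5%: 15.2 + 0.0125 + 20.95 = 36.2, so the SD is 6.0.
- Covariance with the correct score = (1-f)·16 + f·16/8 = 15.2 + 0.1 = 15.3, so the correlation is 15.3/(4 × 6.0) = 0.64.
- The same steps give a correlation of 0.80 at f = 2% and 0.50 at f = 10%.

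A simulation of eight four-level items, with an assumed latent inter-item correlation of 0.3 and 5% of students missing one item, agrees: the SD rises from 4.24 to 5.90 and the regression slope is halved (ratio 0.50). With mean × k, the correlation with the outcome is unchanged.

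**2. Unreversed item.** The most belonging pattern is total disagreement with item 1 and total agreement with items 2 to 8. The least belonging pattern is the opposite.

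- As written: 1 + 7 × 4 = 29 and 4 + 7 × 1 = 11, a spread of 18.
- With item 1 reversed: 8 × 4 = 32 and 8 × 1 = 8, a spread of 24.

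*Illustration with an assumed inter-item correlation of 0.35 and unit item variances.*

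- Correct alpha = 8 × 0.35/(1 + 7 × 0.35) = 0.81.
- Unreversed, 21 of the 28 item pairs are positive and 7 negative, a net 14. The variance is 8 + 2 × 14 × 0.35 = 17.8, and alpha = (8/7)(1 - 8/17.8) = 0.63.
- The correct variance is 8 + 56 × 0.35 = 27.6, and the covariance of the two scores is (7 + 42 × 0.35) - 1 = 20.7. Their correlation is 20.7/√(27.6 × 17.8) = 0.93.

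**3. University expectations.** A tick at any of the four levels of item 3 scores 1, including the most negative one. Only a blank scores 0. No cut-point is given, so the intended binary variable cannot be computed from the table.

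**The case against.** The strongest reply is that these are loose descriptions of sound practice. Since the missing-item sentence contradicts the sum rule for complete responders, it is probably shorthand for filling blanks with the student's own mean before summing, which gives the same score as mean × k. Ticked probably means a positive answer. That reply may well be right about intent, but the table does not say so. For item 1 the table states a direction, and it is the wrong one.

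A reader might infer that the Supplementary 6 results are themselves wrong. The documents do not support that. A rough back-calculation points the other way. Assume PHQ-8 is the outcome, with SD 5.5, about 4,000 students and simple regression. The half-width of 0.04 for School belonging then implies an exposure SD of about 4.3 (3.6 to 5.4 for SD 5 to 6.5 and N 4,600 to 3,500), below the 6.0 computed above for 5% missing. The interval for university expectations (-0.81 to 0.08) implies a smaller category of about 18% (12% to 37%), which looks more like a real cut-point than a record of blanks. This is indicative only.

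A reader might also infer that the trial's intermediate outcomes, "individual-level school engagement (alpha=0.74); career/educational aspirations", are mis-scored. The link is possible but not shown. Outcome measures gives one alpha for school engagement, whereas Supplementary materials 3 has four scales from the Beyond Blue questionnaire, which is not among the sources cited there for the intermediate outcomes. Supplementary material 4 labels a secondary analysis. The trial's data dictionary, mentioned under Data management and analysis, is not part of the documents. The university item comes from RIPPLE and is the likeliest overlap. Intermediate outcomes are in any case exploratory and reported without P values.

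Two further inferences should not be drawn. The PHQ-8 row ends in a stray character and may have lost its missing-item rule in extraction. A limit tighter than two missing items would be a matter of preference.

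**Conclusion.** The point holds as a fault in the documented rules. As written, they misdirect one item of School belonging, put complete and incomplete responders on different scales in all four school scales, and define university expectations by whether the item was answered. The exact consequences are a spread of 18 instead of 24, a score of 3 instead of 24, 12, 18 or 30, and a 1 for a firm no. These follow from the text alone.

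The effect on any estimate is unknown. The SDs, correlations and alphas above rest on assumed means, missingness and inter-item correlations. Whether the analysis code followed the table is also unknown. The reach is limited to the exposures in the secondary analysis, so this should be corrected but does not threaten the trial's main conclusions.

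**What to change.** In the table and the data dictionary:

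1. Reverse School belonging item 1 (5 minus the response) before scoring.
2. For every student within the stated missing limit, score each school scale as the mean of completed items times the number of items, and drop the separate sum and mean sentences.
3. Code university expectations from the response level of item 3, for example definitely or probably will = 1 and probably or definitely will not = 0, or state the cut-point actually used. Set blanks to missing.

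Then check the scoring code behind Supplementary materials 6. If it already followed these rules, say so and correct only the table. If it did not, re-run the models. The cost is a few lines of text and code, plus the re-run if one is needed.

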**SUPPLEMENTARY MATERIAL 4: POSITIVE CHOICES RCT AND SECONDARY ANALYSIS PARTICIPANT FLOW**

Schools invited

N=2845

Schools not recruited

N=2795

Schools recruited and signed consent form to participate

N=50

Schools allocated to control

N=23

Endline student response rate = 3146/4035 (78.0%)

Schools allocated to intervention

N=22

Endline student response rate = 3122/4010 (77.9%)

Schools allocated to intervention but dropped out

N=1

Schools allocated to intervention

N=24

Baseline student response rate (pre-allocation) = 3578/4511 (79.3%)

Schools allocated to control

N=25

Baseline student response rate (pre-allocation) = 3392/4506 (75.3%)

Schools allocated to control but dropped out

before endline N=2

Schools allocated to intervention but dropped out before endline

N=2

Combined intervention and control samples

Overall endline student response rate = 6268/8035 (78.0%)

Students matched to baseline response

Matching rate = 4601/6268 (73.4%)

Students with no corresponding baseline response

Non-match rate: 1667/6268 = 26.5%

Outcome applicable and completed question on outcome (see Table 3 - Overall Sample Size-)

Outcome not applicable or did not complete question

Complete data for all variables in model (see Table 3 - Sample size)

Missing data for at least one variable in model

**Identification**

**Consent**

**Follow-up survey: 33 months**

**Allocation**

**Secondary analysis**

**SUPPLEMENTARY MATERIALS 5: COMPARISON OF STUDY SCHOOLS WITH NON-RECRUITED SCHOOLS IN STUDY AREAS AND SECONDARY SCHOOLS IN ENGLAND**

| **Measure** | | **Positive Choices trial schools** | | **Non-recruited schools^1^** | | **Comparison of recruited and non-recruited schools** | **All-England^2^** | |
| --- | --- | --- | --- | --- | --- | --- | --- | --- |
|  |  | *Schools contributing data N* | *Mean (SD) or*  *N (%)* | *Schools contributing data N* | *Mean (SD) or*  *N (%)* | *p-value* | *Schools contributing data N* | *Mean (SD) or*  *N (%)* |
| Local deprivation (IDACI)^3^ | | 49 | 0.126 (0.098) | 2796 | 0.142 (0.104) | 0.285 | 4083 | 0.148 (0.109) |
| School population size^4,5^ | | 49 | 1072 (424) | 2755 | 928 (481) | 0.038 | 4004 | 920 (479) |
| Students with special educational needs and disabilities (%)^6,7^ | | 49 | 12.9 (4.9) | 2751 | 13.0 (8.9) | 0.938 | 4000 | 13.0 (9.1) |
| Students with English as an additional language (%)^6,7^ | | 47 | 16.8 (16.8) | 2108 | 20.1 (20.1) | 0.264 | 3126 | 17.3 (19.2) |
| Students eligible for free school meals (any time during past 6 years) (%)^6,7^ | | 47 | 23.0 (14.3) | 2108 | 24.7 (14.1) | 0.414 | 3126 | 25.8 (14.3) |
| School Attainment 8 score^7,8^ | | 45 | 47.6 (8.9) | 1917 | 48.4 (9.2) | 0.564 | 2826 | 47.8 (8.9) |
| School Progress 8 score^7,8^ | | 45 | -0.01 (0.42) | 1910 | 0.08 (0.44) | 0.179 | 2818 | 0.03 (0.44) |
| Student absence rate (overall) (%)^5^ | | 46 | 5.6 (1.1) | 2022 | 5.4 (1.2) | 0.263 | 2981 | 5.5 (1.3) |
| School Ofsted rating^7,9^ | *Outstanding* | 47 | 7 (14.9%) | 2144 | 342 (16.0%) | 0.845 | 3195 | 449 (14.1%) |
|  | *Good* |  | 31 (66.0%) |  | 1176 (54.9%) | 0.130 |  | 1654 (51.8%) |
|  | *Requires*  *improvement* |  | 4 (8.5%) |  | 230 (10.7%) | 0.626 |  | 400 (12.5%) |
|  | Not available | 5 | 10.6 | 396 | 18.5 | 0.170 | 650 | 20.3 |
| School sex makeup^5^ | *Mixed sex* | 49 | 43 (87.8%) | 2804 | 2340 (83.5%) | 0.421 | 4091 | 3473 (84.9%) |
|  | *Girls only* |  | 4 (8.2%) |  | 296 (10.6%) | 0.588 |  | 381 (9.3%) |
|  | *Boys only* |  | 2 (4.1%) |  | 168 (6.0%) | 0.576 |  | 237 (5.8%) |

1 Non-recruited schools are mainstream state-funded or private secondary schools including years 8-11 in English local authority areas from which trial recruited.

2 All-England data are for mainstream state-funded and private secondary schools in England including years 8-11.

3 IDACI data were taken from <https://imd-by-postcode.opendatacommunities.org/imd/2019>, accessed 04/02/2022.

4 Excludes schools with population size listed as “0.”

5 Data on school population, Ofsted ratings and school sex make up were taken from get-information-schools.service.gov.uk, accessed 27/01/2022.

6 Data on SEN support, English as an additional language and free school meals for 2020-2021 were taken from www. <https://www.compare-school-performance.service.gov.uk/download-data>, accessed 01/27/2022.

7 Statistics for state-funded schools only

8 Due to the Covid-19 pandemic, data from 2018-2019 were the latest available for Attainment 8 score, Progress 8 score and absence. These were taken from [compare-school-performance.service.gov.uk/download-data](http://www.compare-school-performance.service.gov.uk/download-data), accessed on 25/01/2022 (absence data) and 27/02/2022 (Attainment 8 and Progress 8 scores).

9 Proportions for England Ofsted sum to <100% because data also include 42 schools (1.3%) categorised as “Serious weakness” or “Special measures”

**SUPPLEMENTARY MATERIALS 6: MULTIPLY IMPUTED ANALYSES OF MODELS CONTROLLING FOR SCHOOL AND STUDENT CHARACTERISTICS (MODEL 2)**

| Exposure | | Beta coefficient (unimputed) | Beta coefficient (imputed) |
| --- | --- | --- | --- |
| Student exposures | School belonging | **-0.29**  **(-0.33, -0.25)** | **-0.29**  **(-0.33, -0.25)** |
|  | Educational commitment | **-0.41**  **(-0.50, -0.32)** | **-0.42**  **(-0.50, -0.33)** |
|  | School participation | **-0.25**  **(-0.30, -0.19)** | **-0.25**  **(-0.30, -0.19)** |
|  | Teacher relationships | **-0.16**  **(-0.19, -0.12)** | **-0.15**  **(-0.18, -0.12)** |
|  | University expectation | -0.37  (-0.81, 0.08) | -0.37  (-0.80, 0.07) |
|  | Family affluence | **-0.17**  **(-0.27, -0.08)** | **-0.16**  **(-0.26, -0.06)** |
| School exposures | School belonging | -0.16  (-0.47, 0.15) | -0.18  (-0.47, 0.11) |
|  | Educational commitment | **-1.02**  **(-1.86, -0.18)** | **-0.88**  **(-1.68, -0.08)** |
|  | School participation | -0.11  (-0.47, 0.24) | -0.13  (-0.47, 0.22) |
|  | Teacher relationships | -0.13  (-0.29, 0.03) | -0.11  (-0.27, 0.05) |
|  | University expectations | -1.82  (-4.97, 1.33) | -2.65  (-5.56, 0.25) |
|  | Family affluence | -0.05  (-0.38, 0.29) | -0.02  (-0.35, 0.31) |
